#### Severity

Assessing Adverse Events by Intensity

| **Intensity Level** | **Definition** |
| --- | --- |
| Mild | Discomfort noticed but no disruption of normal daily activity |
| Moderate | Discomfort sufficient to reduce or affect daily activity |
| Severe | Inability to work or perform normal daily activity |
| Life-Threatening | Represents an immediate threat to life |

#### Relationship

Assessing Adverse Events by Relationship to Study Drug Administration

Relationship of an AE to treatment should be assessed using the following terms:

**YES** (Related to test drug)

**NO** (unrelated to test drug)

### Laboratory Test Abnormalities

Laboratory test results will be recorded on the laboratory results pages of the Case Report Form, or appear on electronically produced laboratory reports submitted directly from the central laboratory, if applicable. Laboratory test value abnormalities as such should not be reported on the AE page of the CRF as adverse events unless there is an associated clinical condition for which

a) it is considered to be a Serious Adverse Event (SAE), or

b) the patient is permanently discontinued from study drug because of the abnormal test value, or

c) results in a requirement for additional concomitant treatment or a modification of current concomitant treatment already given for a laboratory abnormality noted at screening/baseline

Neutropenia, thrombocytopenia and anemia should only be reported as an Adverse Events if the following criteria are fulfilled:

**Neutropenia < 500 cells/mm3**

**Thrombocytopenia < 25,000 cells/mm3**

**Anemia < 8.5 g/dl**

The frequency of laboratory test abnormalities have been thoroughly documented in previous development trials.

## Handling of Safety Parameters

### Serious Adverse Events

Any clinical adverse event or abnormal laboratory test value that is *serious* occurring during the course of the study, irrespectively of the treatment received by the patient, must be reported to the National Health Authority adhering to local requirements. The definition and reporting requirements of the ICH Guideline for Clinical Safety Data Management, Definitions and Standards for Expedited Reporting, Topic E2 will be adhered to.

A **serious** adverse event is any experience that suggests a significant hazard, contraindication, side effect or precaution. With respect to human clinical experience, this includes any experience which

• is fatal or life-threatening;

• requires inpatient hospitalization or prolongation of an existing hospitalization;

• results in persistent or significant disability/ incapacity;

• is a congenital anomaly/ birth defect;

• is medically significant or requires intervention to prevent one or other of the outcomes listed above

Medical and scientific judgment should be exercised in deciding whether expedited reporting is appropriate in other situations, such as important medical events that may not be immediately life-threatening or result in death or hospitalization but may jeopardize the patient or may require intervention to prevent one of the outcomes listed in the definitions above. These situations should also usually be considered serious.

The term **severe** is a measure of **intensity**, thus a severe adverse event is not necessarily **serious**. For example, nausea of several hours’ duration may be rated as severe, but may not be clinically serious.

A **death** occurring during the study or which comes to the attention of the investigator within 4 weeks after stopping the treatment or during the 24 weeks of protocol-defined follow-up period, whether considered treatment-related or not, must be reported.

Any pregnancy occuring during a clinical study with an investigational drug must be reported as an SAE for tracking purposes. All pregnancies identified during this study need to be followed to conclusion and outcome reported.

Female patients should immediately inform the Investigator of any pregnancies and should be instructed by the Investigator to stop taking study medication. (Pregnancies occurring up to 6 months after the completion of the study must also be reported to the Investigator). The Investigator should counsel the patient, discuss the risks of continuing with the pregnancy and the possible effects on the fetus. Monitoring of the patient should continue until the conclusion of the pregnancy.

Pregnancy occurring in the partner of a patient participating in the study should also be reported to the Investigator. (Please refer to section 8.2.4 and 8.5)

Such preliminary reports will be followed by detailed descriptions later, which will include copies of hospital case reports, autopsy reports and other documents when requested and applicable.

For serious and all other AEs, the following must be assessed and recorded on the AE page of the CRF: intensity, relationship to test substance, action taken regarding test substance, and outcome to date.

The investigator must notify the Institutional Review Board (IRB) (Independent Ethics Committee (IEC)) of such an event in writing as soon as is practical and in accordance with international and local laws and regulations.

Note: The definitions for and procedures for reporting SAEs to Health Authorities will be taken from the ICH guidelines.

**All SAEs should be faxed to your local Roche office for notification**

ROCHE LOCAL COUNTRY CONTACT for SAEs

**Please specify:**

### Treatment and Follow-up of Adverse Events

Adverse events, especially those for which the relationship to test drug is “yes”, should be followed up until they have returned to baseline status or stabilized. If the use of medications excluded by the protocol are deemed necessary, the patient may need to be discontinued from the test regimen after consultation with Roche.

### Follow-up of Abnormal Laboratory Test Values

In the event of unexplained abnormal laboratory test values, the tests should be repeated immediately and followed up until they have returned to the normal range and/or an adequate explanation of the abnormality is found. If a clear explanation is established it should be recorded on the CRF.

### Pregnancy

Pregnancy is to be strictly avoided during the course of this trial. However, if a female subject becomes pregnant during the study she must be instructed to stop taking the trial medication and immediately inform the investigator. Pregnancies occurring up to 24 weeks after the completion of the trial medication must also be reported to the investigator. The investigator should counsel the subject, discuss the risks of continuing with the pregnancy and the possible effects on the fetus. Monitoring of the patient should continue until conclusion of the pregnancy.

Pregnancy occurring in the partner of a male patient participating in the study should also be reported to the investigator. The partner should be counseled and followed as above. Such patients may not continue to receive ribavirin.

***Please also refer to section 8.5 “Warnings and Precautions”!***

## Dose Adjustment Guidelines for Intolerance

The intention of the protocol is that patients demonstrating a response to therapy remain on test drug until the completion of the trial. However, it is possible that some patients will encounter transient or prolonged adverse effects at some juncture during their participation in the trial necessitating test drug dosage adjustment. To minimize the effects of these modifications on the eventual evaluation of the safety, tolerability, and efficacy of test drug regimens, the principles in the following sections will be used to adjust the dose of test drugs.

### PEGASYS® Dose Modifications

If at all possible, doses should not be held or eliminated. This recommendation stems from concerns that extended periods of lowered drug concentrations in the blood may be associated with the replication of the more resistant clones of the virus, resulting in a lack of sustained response at the conclusion of therapy.

Specific dose adjustment guidelines for PEGASYS® are provided in appendix 2 for neutropenia, thrombocytopenia and elevated serum ALT activities.

For other adverse effects considered to be possibly related to PEGASYS®, including laboratory abnormalities, adverse events, and vital signs changes, investigators should utilize section 8.3.1.1 below labeled “General Dose Reduction Guidelines”. When practicable, abnormal laboratory results should be confirmed as soon as possible following notification of the investigator. If appropriate, downward adjustments in one level increments should be considered. The lowest dose of PEGASYS® that should be administered is 45 mg. It should be kept in mind that whereas these guidelines should be generally followed to promote consistency across centers, other responses by an investigator may be more appropriate in some circumstances.

Once the patient’s unit dose has been decreased, the investigator may attempt to increase the dose back to or towards that originally assigned if the event or circumstance responsible for the dosage adjustment has resolved or improved.

**If one week or more of PEGASYS**® **dosing is missed (or changed), that information must be recorded on the Case Report Form.**

Decremental adjustments should be uniform across centers and patients. The following downward adjustments should be utilized:

| Assigned Dose | One Level Adjustment | Two Level Adjustment | Three Level Adjustment |
| --- | --- | --- | --- |
| PEGASYS® 180 g | PEGASYS® 135 g | PEGASYS® 90 g | PEGASYS® 45 g |

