### Ribavirin Dose Modifications

If the ribavirin concentration measured on day 28 in Groups A and B is below the target concentration (2.5 mg/L (10.25 mol/L)), the dose of ribavirin should be increased as soon as possible preferably within 2 weeks of measuring the ribavirin concentration if the patient can tolerate an increase. The new recommended dose is the previously given dose divided by the concentration of ribavirin measured multiplied by the target concentration (2.5 mg/L (10.25 mol/L)) (see Appendix 3).In the event of a change in ribavirin dosing in Groups A (“Loading”) and B (“Priming”), a new local ribavirin concentration should be evaluated after 4 weeks. Ribavirin should be administered twice-daily with food.

Where dose reduction is required stepwise incremental adjustments of 200 mg (1 tablet) should be utilized where clinical circumstance allows.

If either of the following is confirmed, it is recommended that the ribavirin dose should be reduced, at the discretion of the investigator dependent on local treatment guidelines:

- A patient without significant cardiovascular disease experiences a fall in hemoglobin to <10 g/dL (<100 g/L) and >8.5 g/dL (>85 g/L) or
- A patient with stable cardiovascular disease experiences a fall in hemoglobin by >2 g/dL (>20 g/L) during any 4 weeks of treatment

For the purposes of this protocol, patients with “stable cardiovascular disease” include not only patients with known, stable cardiac and vascular disorders, but also patients with major cardiac risk factors including hypertension and diabetes mellitus.

Patients who have more than a 3 g/dL (30 g/L) decrease from baseline in their Hgb concentration should have an appropriate work-up for anemia, including reticulocyte count, search for sources of bleeding, etc.

Moreover, ribavirin should be discontinued under the following circumstances:

- If a patient without significant cardiovascular disease experiences a fall in hemoglobin confirmed to be less than 8.0 g/dL (80 g/L).
- If a patient with stable cardiovascular disease maintains a hemoglobin value <12 g/dL (<120 g/L) despite 4 weeks on a reduced dose of 600 mg.

Ribavirin monotherapy is not allowed; in the event that PEG-IFN alfa-2a treatment has to be permanently discontinued the patient must cease all study medications and must be followed for safety reasons for at least 12 weeks.

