## Statistical and Analytical Methods

### Analysis Plan

This is a pilot trial with the viral kinetic response and SVR measured as described above, during the first 12 weeks of therapy as primary endpoint with the aim of investigating the feasibility and safety of “loading” and “priming” dosing of ribavirin in conjunction with PEG-IFN for chronic HCV genotyp 1. Intention-to-treat and Per-protocol analysis on primary endpoints will be performed for patients receiving at least one dose of the study drugs. Additionally, an analysis of SVR with regards to whether or not the target concentration of ribavirin 2.5 mg/L (10.25 μmol/L) at day 28 was achieved across all study arms will be performed.

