#### Definition of Analysis Populations

**Intent-to-treat analysis population** is defined to include all patients who received at least one dose of study medication. Except for change from baseline parameters, the primary and all other secondary efficacy parameters will be analyzed using the intent-to-treat population.

**Per-protocol** **analysis population** is defined to include all patients who received ≥80% of both planned Pegasys and Copegus dose for ≥80% of planned treatment duration.

**Standard analysis (per-protocol) population** will exclude a patient if the patient meets any of the exclusion criteria listed in Section 9.2.2.2. Analysis using the standard population will be performed only if > 5% of patients are excluded from one of the treatment groups.

**Safety analysis population** is defined to include only patients who receive at least one dose of (either) study medication and have at least one post-baseline safety assessment.

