#### Exclusion of Data from Analysis

The following patients will be excluded from the standard (per protocol) analysis:

1. Patients who never took any study medication.
2. Patients on PEGASYS® who received ≤80% of both planned PEGASYS®  and COPEGUS® dose for ≤80% of planned treatment duration.
3. Patients with no post-baseline HCV-RNA assessment.

The following patients will be excluded from the safety analysis:

1. Patients who never took any study medication.
2. Patients without any post-baseline safety assessment.

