Appendix 2 PEGASYS Dose Adjustment Guidelines

Specific dose adjustment guidelines for PEGASYS are provided below for post-treatment, neutropenia, thrombocytopenia, elevated serum ALT activities, and depression. It should be kept in mind that other responses by an investigator, in accordance with local guidelines, may be more appropriate, and that an investigator does not have to abide by the dose adjustment guidelines listed below. For other adverse effects considered to be related to PEGASYS, including laboratory abnor­malities, adverse events, and vital sign changes, investigators should utilize the table below labeled “PEGASYS General Dose Reduction Guidelines.” When practicable, abnormal laboratory results should be confirmed as soon as possible following notification of the investigator. If appropriate, downward adjustments in one level decrements (see section 7.3.1) should be considered. The lowest dose of PEGASYS that should be administered is 45 µg. For laboratory and vital signs abnormalities, “severe” is defined as any value requiring intervention, further work-up, or more frequent follow-up.

PEGASYS General Dose Reduction Guidelines

| **Number of Dose Reduction Levels (see Section 7.3.1)** | | | | | |
| --- | --- | --- | --- | --- | --- |
| **Mild** | **Moderate**  **Limited** | **Moderate**  **Persistent** | **Severe**  **Limited** | **Severe**  **Persistent** | **Life-Threatening** |
| 0 | 0 | 0-1 | 0-1 | 1-2 | Stop Drug |

Dose Adjustments for Low Absolute Neutrophil Counts

| **ANC** | **PEGASYS Dose Reduction** |
| --- | --- |
| < 750 cells/mm3 | 135 µg |
| < 500 cells/mm3 | Withhold treatment until ANC returns to >1000 cells/mm3. Resume treatment at 90 µg and monitor ANC |

Dose Adjustments for Low Platelet Counts

| **Platelet Count** | **PEGASYS Dose Reduction** |
| --- | --- |
| < 50.000 cells/mm3 | 90 µg |
| < 25.000 cells/mm3 | Withhold treatment |

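### The 80/80 per-protocol rule can exclude patients for sustained dose reductions made under the protocol's own toxicity guidance, even after the week-12 outcome is complete

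*Protocol*

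**What the plan says.** **Dose reductions.** Protocol 8.3 states that "the principles in the following sections will be used to adjust the dose of test drugs". Section 8.3.1 introduces its table with "The following downward adjustments should be utilized" and lists levels of 135, 90 and 45 µg from an assigned 180 µg. It allows the dose to be raised again once the problem improves. Appendix 2 ties levels to laboratory limits, for example "< 750 cells/mm3 | 135 µg", but also says that investigators need not follow the guidelines. For ribavirin, 8.3.2 says "stepwise incremental adjustments of 200 mg (1 tablet) should be utilized" where circumstances allow, and leaves the decision to reduce to the investigator. In Groups A and B only, 8.3.2 and Appendix 3 also provide for an increase when the day-28 concentration is below target.

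**Analysis sets.** Section 9.2.1 says "Intention-to-treat and Per-protocol analysis on primary endpoints will be performed for patients receiving at least one dose of the study drugs". Section 9.2.1.1 defines the per-protocol population as "all patients who received ≥80% of both planned Pegasys and Copegus dose for ≥80% of planned treatment duration". The same section names a second set, a standard set that is also labelled per-protocol. It is defined by the exclusion list in 9.2.1.2 and analysed only if more than 5% of patients are excluded from a treatment group. Item 2 of that list removes patients who had at most 80% of both drugs, ending "COPEGUS® dose for ≤80% of planned treatment duration".

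**Time frame.** The primary variable is the HCV-RNA decline over the first 12 weeks (6.1, 9.1.1). The sample size in 9.3 uses days 0 to 3 and days 7 to 28. Planned combination treatment is 24 or 48 weeks, with 72 weeks possible for some patients (7.5 Treatment Duration).

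**The concern.** A per-protocol set should remove patients who departed from the protocol. Here the dose limit lies above the first PEGASYS reduction level, and above the first ribavirin step in the lightest weight band. Neither section makes an exception for changes made under 8.3, and neither says what the planned dose is after a reduction or a concentration-targeted increase. A patient treated within the guidance can therefore be classed as not per protocol.

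The exposure window adds to this. It covers the whole course, while the primary outcome ends at week 12. Exclusion for a reduction at, say, week 15 cannot reflect anything that influenced the outcome being analysed; it selects on later tolerability. Tolerability may itself depend on the randomised ribavirin regimen, so the A-C and B-C per-protocol comparisons could lose the balance given by randomisation as well as patients.

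**Working it through.** The protocol states no percentage for any dose step, so there is no figure of its own to reproduce. The inputs are the levels in 8.3.1 and 8.3.2, the doses in Appendix 3, the durations in 7.5 and the limit in 9.2.1.1.

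**Step 1: dose fractions (reduced dose / assigned dose).**

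- PEGASYS: 135/180 = 75%; 90/180 = 50%; 45/180 = 25%. All are below 80%.
- Ribavirin, one 200 mg step from the standard dose:

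| Weight | Fraction | Against 80% |
|---|---|---|
| 45-60 kg | 600/800 = 75.0% | below |
| 61-75 kg | 800/1000 = 80.0% | exactly at the limit |
| 76-90 kg | 1000/1200 = 83.3% | above |
| 91-105 kg | 1200/1400 = 85.7% | above |

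The 61-75 kg result satisfies the dose condition for inclusion in 9.2.1.1 and also meets the dose limit for exclusion in 9.2.1.2. One step from the Group A loading dose leaves 1400/1600 = 87.5% up to 2600/2800 = 92.9%, above the limit in every band.

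**Step 2: time-based reading.** Time at 80% dose or more must be at least 80% of the duration T. A cut to 75% excludes only if it lasts more than 0.2 × T: 0.2 × 24 = 4.8 weeks, or 0.2 × 48 = 9.6 weeks. A lasting PEGASYS cut that starts after week 12 therefore still excludes if it starts before week 19.2 of 24 or week 38.4 of 48.

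**Step 3: cumulative reading.** With a lasting cut to fraction f from week t, the share received is (t + f(T − t))/T. Setting this to 0.8 gives t = T(0.8 − f)/(1 − f).

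- f = 0.75: t = 0.2T, so exclusion only if the cut starts before week 4.8 of 24 or 9.6 of 48. A cut from week 12 of 48 gives (12 + 0.75 × 36)/48 = 81.25%, and the patient stays in.
- f = 0.50: t = 0.6T = 14.4 or 28.8 weeks. A lasting two-level PEGASYS cut can therefore exclude after week 12 on this reading too.

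**Step 4: is there a built-in arm difference?** PEGASYS levels are the same in all arms, and so are the starting ribavirin doses after day 14. For a lasting ribavirin cut from 800 to 600 mg on the cumulative reading, the patient stays in if the cut starts at or after these weeks of PEG-IFN:

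- C: 0.2T = 4.8 (T = 24) or 9.6 (T = 48).
- A, planned total 800(T + 2) in daily-dose weeks: T − 0.8(T + 2) = 3.2 or 8.0.
- B, planned total 800(T + 4): T − 0.8(T + 4) = 1.6 or 6.4.

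The same cut is thus tolerated slightly better in A and B than in C. One asymmetry can work the other way. Suppose a Group A or B patient on 800 mg has a concentration of 1.67 mg/L (an assumed value). The formula in 8.3.2 gives 800/1.67 × 2.5, about 1200 mg. A later return to 800 mg is 67% or 100% of the planned dose, depending on which dose counts as planned. This cannot arise in C.

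**Step 5: illustrated bias (assumed inputs only).** Let viral decline have correlation r with the need for a disqualifying reduction, and let 40% of A and 20% of C be excluded. For a standard normal z truncated above at its 60% and 80% quantiles, the means are −0.644 and −0.350. Bias = r × (−0.644 + 0.350); with r = 0.4 this is −0.118 SD. Treating the sizing as a comparison of means, 35 per arm with 80% power at one-sided 5% implies a standardised effect of (1.645 + 0.842) × √(2/35) = 0.594. The ratio is 0.118/0.594 = 20%. It is about 10% to 25% for r from 0.2 to 0.5, and about 10% for rates of 30% v 20% with r = 0.4. **With equal rates it is zero.** With 21 v 28 patients left, 0.594/√(1/21 + 1/28) − 1.645 = 0.41, a power of about 66%.

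**The case against.** The strongest reply is that an 80/80 rule is a reasonable definition of adequate exposure, that intention-to-treat is also run on the primary endpoints, and that the details of planned dose are commonly left to the SAP, which is not at hand. If planned means the dose after adjustment, most of the problem disappears. Part of this stands: an exposure set is legitimate if it is labelled as one, and the consequence is confined to the per-protocol analysis. But the protocol itself fixes the limit and the full-course window, and calls the result per-protocol. Section 9.2.1.1 also excepts change-from-baseline parameters from intention-to-treat, which sits awkwardly with a primary variable that is a decline.

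Item 2 of 9.2.1.2, read literally, requires both drugs to be at or below 80%, so reducing one drug alone would exclude nobody from the standard set. That is correct. It means that the same patient is in or out depending on which definition is used.

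The reductions are also guidance and partly discretionary, so it is too much to say that excluded patients did exactly what was ordered. They were managed within the guidance.

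Three stronger inferences are not supported:

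- *That any PEGASYS cut before week 19.2 or 38.4 excludes.* Only lasting cuts do so, and only on the time-based reading. Re-escalation is allowed.
- *That exclusions are unequal by arm.* The documents give no reduction rates by arm. A difference is plausible, because anemia is described as ribavirin's primary toxicity with hemoglobin falls mostly in the first 1-2 weeks, when Group A has the doubled dose, and because only A and B have concentration-targeted increases. Its size and direction are unknown.
- *That the weight-band threshold biases the comparison.* Weight is a baseline characteristic under randomisation, so a threshold by weight does not by itself favour an arm.

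**Conclusion.** The point holds as a defect in how the per-protocol population is defined. Every PEGASYS reduction level (75% or lower) and one ribavirin step at 45-60 kg (75%) are below the 80% limit, and there is no exception for reductions made under 8.3. A sustained reduction can therefore remove a patient: after more than 4.8 of 24 or 9.6 of 48 weeks at the lower dose on the time-based reading, or with a lasting cut to 75% that starts before those weeks on the cumulative reading. On the time-based reading this can happen after the day 0-3, day 7-28 and week-12 outcomes are complete. The per-protocol analysis of the primary endpoints then selects on later tolerability.

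The dose fractions and week limits follow from the protocol's own figures. The bias does not. The 20% illustration rests on assumed exclusion rates and an assumed correlation, and the range has to include zero. The 66% is likewise conditional on those rates; the protocol states its 80% for 35 patients per arm, not for the per-protocol set.

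**What to change.** In 9.2.1.1 and item 2 of 9.2.1.2:

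1. Reconcile the two rules into one definition, settling whether one drug or both must fall short, how exactly 80% is treated, and whether the limit applies to time at dose or to cumulative dose.
2. For the primary endpoints, assess exposure only up to the time of the endpoint (through week 12), against the dose prescribed at each time under 8.3 and Appendices 2-3. Protocol-directed reductions, interruptions and concentration-targeted increases are then not deviations; missed doses and changes outside those provisions are.
3. Keep the present 80/80 rule over the full course as a separate sensitivity set, labelled full exposure.
4. Tabulate dose reductions by arm, so that any imbalance is seen rather than assumed.

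The cost is wording. Missed and changed doses are already to be recorded in the CRF (7.4, 8.3.1, 8.3.2). The downside is that the per-protocol set will include some patients with lower exposure, including some whose ribavirin was stopped under the protocol, and so moves closer to intention-to-treat; the full-exposure set answers the other question. No dose or clinical rule changes.
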